## Abstract

**Background/Objectives:**

Acute Low Back Pain (LBP) commonly shows rapid symptom improvement during the early phase; however, delayed or inadequate treatment may increase the risk of recurrence and chronicity. Ultrasound-guided pharmacopuncture has demonstrated promising analgesic effects, yet the optimal needle length for deep interfascial targeting remains unclear, particularly in procedures involving the Quadratus Lumborum–Psoas–Iliocostalis (QPI) space. This study aims to compare the short-term clinical response, procedural feasibility, and safety of short versus long needles used for QPI-guided pharmacopuncture in patients with acute LBP.

**Methods:**

This prospective, multicenter, comparative observational study includes adults aged 20–65 years presenting with acute LBP within 7 days of onset. Participants undergo a single session of ultrasound-guided Polydeoxyribonucleotide (PDRN) pharmacopuncture targeting the QPI interfascial plane using either a short needle (26G × 60 mm) or a long needle (25G × 100 mm). Group assignment is based on pre-designated site-level data extraction rather than randomization. The primary outcome is the change in the Numeric Rating Scale (NRS) score immediately after treatment. Secondary outcomes include changes in lumbar range of motion (ROM), patient-reported percentage pain reduction (PRPPR), and procedural usability. Safety is monitored immediately post-procedure and again during a telephone follow-up 24–36 h later. Statistical analyses will compare between-group effects and explore potential associations with procedural characteristics.

**Discussion and conclusion:**

This study aims to provide preliminary feasibility evidence on whether needle length affects procedural performance and immediate analgesic response during ultrasound-guided interfascial pharmacopuncture for acute LBP. By evaluating both clinical and procedural metrics, the results may contribute to establishing standardized needle-selection criteria and support future randomized controlled trials designed to optimize deep pharmacopuncture techniques within Korean medicine primary care settings.

**Clinical trial registration:**

https://cris.nih.go.kr/cris/search/detailSearch.do?seq=32507&search_page=L&search_lang=&class_yn=.

## Introduction

1

Low back pain (LBP) is one of the most prevalent musculoskeletal disorders worldwide and is a major contributor to reduced quality of life and increased socioeconomic burden. In Korea, the number of patients seeking care for LBP has continued to rise, along with the growing demand for Korean medicine-based treatments. According to the *2023 Yearbook of Korean Medicine,* published in 2025 (1), the two conditions accounting for the highest proportion of outpatient expenditures in Korean medicine institutions in 2023 were back pain and lumbar sprain, underscoring the high clinical demand for LBP-related care.

The number of patients seeking care for LBP and lumbar sprain at both Korean medicine and conventional medical institutions has remained consistently high in Korea (2). These figures indicate that a substantial proportion of patients with LBP utilize Korean medicine services, highlighting the need for further standardization of interventional procedures in Korean medicine clinical practice.

Acute LBP typically shows rapid improvement within the first 6 weeks; however, recovery significantly slows thereafter (3). Despite initial improvement, symptoms often fail to resolve completely, and approximately 32% of patients with acute LBP progress to chronic LBP within 6 months (4). This transition to chronic phase is associated with higher recurrence rates, reduced quality of life, increased healthcare utilization, and substantial societal costs. Therefore, accurate assessment and timely intervention during the acute phase are critical for favorable long-term outcomes, as insufficient management of early pain increases the risk of recurrent exacerbations and chronicity.

Pharmacopuncture, a Korean medicine intervention that combines acupuncture with bioactive pharmacological agents, has demonstrated rapid analgesic effects in acute LBP, lumbar sprain, and myofascial pain syndrome. Various conservative interventions for LBP, including pulsed electromagnetic field therapy, have also been investigated for pain reduction and functional improvement in previous studies (5). Recently, ultrasound-guided pharmacopuncture has gained attention due to its ability to deliver agents precisely to the targeted anatomical structures while avoiding major nerves and blood vessels (6, 7). A recent systematic review reported that ultrasound-guided pharmacopuncture provides superior pain relief and functional improvement compared with non–image-guided procedures, including an additional 27% improvement in pain outcomes in subgroup analyses focusing on lumbar conditions (8).

However, deep lumbar interfascial structures—such as those surrounding the Quadratus Lumborum(QL) and Psoas Major(PM)—present significant technical challenges due to anatomical variability, soft tissue thickness, and reduced needle-tip visibility at greater depth (9). Conventional 60-mm needles may be insufficient for reliably reaching deep target layers, whereas longer needles (e.g., 100 mm) can provide stable access but have not been widely adopted in Korean medicine due to limited evidence regarding their safety and handling characteristics. Furthermore, the physical limitations of ultrasound, particularly reduced echogenicity at greater depth, have led to increasing clinical demand for needle-tracking technology to enhance procedural accuracy (10).

Our research team previously performed ultrasound-guided pharmacopuncture targeting the interfascial space between the QL, PM, and Iliocostalis(IC) muscles—referred to as the “QPI space”—in five patients with acute lumbar myofascial pain. This procedure resulted in significant reductions in pain and improvements in lumbar Range of Motion(ROM), with successful deep-plane access and no adverse events (7). These findings provide preliminary feasibility evidence supporting the need for systematic evaluation of needle length and procedural performance in ultrasound-guided deep pharmacopuncture.

Based on these clinical needs and previous findings, the present study aims to compare the immediate analgesic effects of short versus long needles in ultrasound-guided pharmacopuncture targeting the QPI space through a prospective, multicenter observational design. The primary outcome is the change in pain intensity immediately after treatment, enabling evaluation of how needle length influences the acute-phase clinical response. Additionally, secondary procedural and exploratory metrics—including deep-plane reachability, technical usability, and safety—will be assessed to explore the feasibility and potential for standardizing deep ultrasound-guided pharmacopuncture in primary care Korean medicine settings.

## Materials and methods

2

### Study design

2.1

This prospective, multicenter, comparative observational study aims to evaluate whether needle length (Long versus Short) influences procedural usability, deep target achievement rate, clinical effectiveness, and safety during ultrasound-guided pharmacopuncture for acute LBP. The intervention targets the interfascial plane formed by the QL, PM, and IC muscles—referred to as the “QPI space.” The anatomical location and ultrasound appearance of the QPI interfascial space are illustrated in Figure 1. All procedures are performed under real-time ultrasound guidance. Polydeoxyribonucleotide (PDRN) derived from salmon is used as the pharmacological agent, and a magnetic needle–guided tracking system is applied to deliver 1–2 mL of the injectate into the target layer.

**Figure 1 fig1:**
[figure not shown]
Anatomical structure and ultrasound visualization of the quadratus lumborum–psoas–iliocostalis (QPI) interfascial space. **(A)** Cross-sectional anatomi-cal illustration at the lumbar level demonstrating the anatomical relationship among the quadratus lumborum, psoas major, and iliocostalis muscles. The interfascial plane formed by these muscles, referred to as the QPI space (blue dot), and the intended needle trajectory toward the target layer are illustrated. **(B)** Representative ultrasound image with annotated muscle boundaries corresponding to the anatomical structure, showing the iliocostalis, quadratus lumborum, and psoas major muscles and the intervening QPI interfascial space. **(C)** Corresponding unannotated ultrasound image of the same scanning plane, demonstrating the native sonographic appearance of the QPI interfascial space.

Participants who express willingness to join the study will be screened according to the inclusion and exclusion criteria after receiving a full explanation of the study’s purpose and procedures and providing written informed consent. Eligible participants will be allocated to either the Short Needle Group (SNG; 26G × 60 mm) or the Long Needle Group (LNG; 25G × 100 mm). The two needle types used in this study are shown in Figure 2.

**Figure 2 fig2:**
[figure not shown]
Comparison of the two magnetized needle types used in this study (26G × 60 mm and 25G × 100 mm).

All four participating clinical sites routinely use both types of needles in daily practice, depending on actual clinical circumstances. For the purpose of comparative analysis, two sites will be designated to contribute only cases treated with short needles, while the other two sites will contribute only cases treated with long needles. This approach represents a site-level data extraction scheme, rather than a randomized allocation process, and is designed to enable comparative analysis of procedures performed in routine clinical practice without modification of standard patient care.

The study procedures consist of three stages: screening, the treatment visit (Visit 1), and post-procedure follow-up at 24 to 36 h. After providing written informed consent, participants undergo screening, during which demographic characteristics and relevant medical history are collected, and eligibility is assessed based on predefined inclusion and exclusion criteria. Participants who meet all eligibility criteria proceed directly to Visit 1, during which the ultrasound-guided pharmacopuncture intervention and all corresponding study assessments are conducted.

During Visit 1, all enrolled participants undergo a single ultrasound-guided PDRN pharmacopuncture procedure following a standardized protocol. Prior to the intervention, baseline assessments are conducted, including Numerical Rating Scale (NRS) scores for LBP and radiating leg pain, lumbar ROM, the Oswestry Disability Index (ODI), and the Patient-reported Percentage Pain Reduction(PRPPR) score. After the baseline evaluation, the practitioner identifies the interfascial QPI space using high-resolution ultrasonography and then performs the injection using a magnetically guided needle system, administering 1–2 mL of the PDRN pharmacopuncture solution.

The procedure is performed using an in-plane needle approach, enabling real-time visualization of the needle trajectory and tip through ultrasound imaging combined with a magnetic needle-tracking system. Both groups receive the same injection technique and target the same anatomical site; however, the SNG uses a 26G × 60 mm needle, while the LNG uses a 25G × 100 mm needle. All other procedural variables remain consistent across groups.

During the procedure, performance-related indicators are recorded, including the number of needle insertions, total procedure time, confirmation of needle-tip arrival at the deep target layer (QPI space), and visualization of the hypoechoic spread during injectate delivery. All ultrasound images and needle-tracking log data are stored for subsequent analysis.

Immediately after the procedure, pain intensity (NRS), PRPPR, and ROM are reassessed. Additionally, the operator completes a usability questionnaire to evaluate needle visibility, tracking stability, handling comfort, confidence in target engagement, perceived procedural workload, and overall satisfaction. Any immediate adverse events occurring at this time point are documented in detail.

Follow-up assessments are conducted via telephone within 24 to 36 h after the procedure. During this contact, changes in pain intensity (NRS), PRPPR, functional status in daily activities, and the presence of any delayed adverse events are evaluated. All collected data are recorded using institution-specific Case Report Forms (CRFs) and included in the final analysis after de-identification. A summary of the study procedures is presented in Table 1.

**Table 1 tab1:** Summary of study procedures and assessment timeline.

Study procedure	Period		
	Screening*	Visit 1	F/U^†^
	-1D^‡^	Baseline (0)	~1D
Explanation of the study and obtaining consent	○		
Determination of inclusion/exclusion criteria	○		
Demographic survey^a^	○		
Medical history investigation^b^	○		
ODI (Baseline)^c^		○	
NRS (Pre-/Post-intervention, Day 1)^d^		○	○
PRPPR (Post-intervention, Day 1)^e^		○	○
ROM (Range of Motion) (Pre-/Post-intervention)^f^		○	
Intervention (Short needle vs. Long needle)		○	
Adverse event assessment^g^		○	○

*If the subject is deemed eligible after screening, the first intervention will be performed immediately after obtaining informed consent. ^†^A telephone-based follow-up will be conducted within 1 day (24–36 h) after Visit 1. ^‡^D indicates “Day.” ^a^Demographic survey: information on gender, age, year of birth, height, weight, and other baseline characteristics will be collected. ^b^Medical history: includes previous history of low back pain(LBP), hypertension, diabetes, osteoarthritis, sleep disorders, psychiatric history, current medications, smoking history, and alcohol consumption. ^c^ODI (Oswestry disability index): the ODI is a validated questionnaire assessing functional disability related to LBP. It consists of 10 items covering pain intensity and daily activities, and yields a score ranging from 0 to 100%, with higher scores indicating greater disability. In this study, ODI is administered only at baseline to evaluate initial functional status. ^d^NRS (numeric rating scale): pain intensity for LBP will be assessed on a 0–10 scale, where higher scores indicate more severe pain. ^e^PRPPR (patient-reported percentage pain reduction): subjects will be asked to report the perceived percentage of pain reduction compared with pre-intervention status, on a 0–100% scale, both immediately after treatment and at Day 1 follow-up. ^f^ROM (range of motion): lumbar ROM—including flexion, extension, lateral flexion, and rotation—will be assessed to evaluate functional changes. ^g^Adverse events: adverse events or unexpected symptoms occurring immediately after the procedure or during follow-up will be assessed and recorded.

The study protocol has been submitted for Institutional Review Board (IRB) approval. Ethical approval will be obtained prior to the initiation of participant enrollment. No participants have been recruited or exposed to the intervention at the time of manuscript submission.

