#### Setting

2.3.1

This multicenter study will take place across four Korean medicine clinics that provide primary outpatient care for musculoskeletal conditions. Participant enrollment and all research-related procedures will be conducted in the outpatient setting of each clinic.

The list of four Korean medicine clinics is as follows:

Kangnyung Korean Medicine Clinic (Anyang, Gyeonggi Province, Republic of Korea).Gwanghwamun Kyung Hee Korean Medicine Clinic (Jongno-gu, Seoul Metropolitan City, Republic of Korea).Mullae Majubom Korean Medicine Clinic (Yeongdeungpo-gu, Seoul Metropolitan City, Republic of Korea).Mapo Hongik Korean Medicine Clinic (Mapo-gu, Seoul Metropolitan City, Republic of Korea).

The interventions will be performed exclusively by Korean medicine doctors who have undergone structured training in ultrasound-guided pharmacopuncture and who are active members of the Academy of Korean Medicine Clinical Anatomy, an organization specializing in ultrasound-based clinical anatomy research.

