#### Inclusion criteria

2.3.2

Participants will be included if they meet all of the following conditions:

Age between 20 and 64 years.Acute LBP within 7 days of symptom onset, accompanied by lumbar pain and limited ROM.LBP, with or without referred leg pain.No prior treatment for the current episode of LBP (diagnostic imaging alone is permitted).Ability to understand the study procedures and provide written informed consent.Participants treated with ultrasound-guided pharmacopuncture using a long needle (25G × 100 mm) at Mapo Hongik Korean Medicine Clinic or Gwanghwamun KyungHee Korean Medicine Clinic, or using a short needle (26G × 60 mm) at Mullae Majubom Korean Medicine Clinic or Gangnyeong Korean Medicine Clinic.

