#### Statistical analysis

2.6.2

All statistical analyses will be performed using R software (version 4. X. X; R Foundation for Statistical Computing, Vienna, Austria). All tests will be two-tailed, with statistical significance defined as *p* < 0.05. Continuous variables will be summarized as mean ± standard deviation or median with Interquartile Range (IQR), depending on the data distribution. Categorical variables will be presented as frequencies and percentages.

For the primary outcome, changes in NRS scores will be analyzed according to the data distribution. Between-group comparisons will be performed using an independent *t*-test if the normality assumption is satisfied; otherwise, the Wilcoxon rank-sum test will be used. Within-group changes will be assessed using a paired *t*-test or the Wilcoxon signed-rank test, depending on whether the data meet normality assumptions.

For the secondary outcomes, changes in lumbar ROM from baseline will be analyzed using the same statistical methods applied to the primary outcome. Between-group comparisons will be conducted using an independent *t*-test or the Wilcoxon rank-sum test, while within-group comparisons will be analyzed using a paired *t*-test or the Wilcoxon signed-rank test, depending on data normality.

The ODI will be categorized into predefined functional disability levels, and differences in distribution between groups will be analyzed using the Chi-square test or Fisher’s exact test, as appropriate.

PRPPR will be assessed immediately after treatment and again at 24–36 h post-intervention. Between-group comparisons will be conducted using an independent *t*-test or the Wilcoxon rank-sum test, while within-group comparisons will be analyzed using a paired *t*-test or the Wilcoxon signed-rank test, depending on the data characteristics.

In addition, procedural characteristics and usability-related variables associated with needle length—including deep-layer reach success rate, number of insertions, procedure time, and operator usability score—will be summarized using descriptive statistics. When appropriate, exploratory between-group comparisons will be conducted using the Mann–Whitney U test or the Chi-square test. These analyses will serve as supportive reference analyses and will not directly influence the interpretation of the primary clinical outcomes.

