Despite these strengths, this study has several inherent limitations due to its exploratory observational design. First, the site-based allocation approach may introduce selection bias. Second, because the intervention was conducted as a single session with short-term follow-up (24–36 h), the study design does not permit evaluation of sustained or cumulative treatment effects. Third, not all participants underwent imaging-based diagnostic confirmation, which may lead to diagnostic heterogeneity and should be taken into account when interpreting the findings.

Future research should include randomized controlled trials to verify the independent effects of needle length and NGS application, as well as quantitative imaging-based assessments of needle tip visibility and tracking accuracy. Additionally, studies incorporating repeated interventions, long-term follow-up, and subgroup analyses based on BMI, muscle thickness, or pain phenotype may further clarify patient-specific treatment responses. Finally, cost-effectiveness analyses would help determine the practical value of ultrasound-guided interfascial pharmacopuncture in primary care settings and contribute to establishing clearer clinical indications and standardized application criteria for the QPI-guided approach.

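### Needle length is fully aliased with clinic, and no planned analysis can separate the two, yet the protocol attributes the group difference to needle length.

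*Protocol article*

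**What the plan says.** Section 2.1 sets the rule: "two sites will be designated to contribute only cases treated with short needles, while the other two sites will contribute only cases" of the long-needle type. It adds: "This approach represents a site-level data extraction scheme, rather than a randomized allocation process". Section 2.3.2 writes the rule into eligibility, admitting patients treated "using a long needle (25G × 100 mm) at Mapo Hongik Korean Medicine Clinic or Gwanghwamun KyungHee Korean Medicine Clinic" and short-needle patients only at the other two named clinics. Section 2.3.1 confirms the number of centres: "This multicenter study will take place across four Korean medicine clinics". Section 2.1 also says: "All four participating clinical sites routinely use both types of needles in daily practice". That sentence goes on to say that the choice depends on the clinical situation.

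For the primary outcome, Section 2.6.2 states: "Between-group comparisons will be performed using an independent" t-test, or a Wilcoxon rank-sum test if normality fails. Lumbar ROM and PRPPR are handled the same way. For procedural and usability variables it says: "When appropriate, exploratory between-group comparisons will be conducted using the Mann–Whitney U test or the Chi-square test", and calls these analyses supportive only. No test has a clinic term. The last paragraph of Section 2.6.2 adds ANCOVA, regression or subgroup analysis only for baseline variables that differ significantly between groups and may relate to outcome. Clinic and operator are not named.

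Section 2.1 gives the aim as finding out whether needle length influences usability, target achievement, effectiveness and safety, and Section 2.5.1 repeats this for the change in NRS. Among the limitations, Section 3 says: "First, the site-based allocation approach may introduce selection bias", and it calls for future randomised trials of the independent effect of needle length.

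**The concern.** Anything that differs between the two pairs of clinics is carried in full into the needle contrast: patient mix, how the NRS is asked, how the goniometer is read, local practice. If operators and assessors each work at one clinic, their effects are carried in as well, and a usability difference could be a difference between raters. The protocol does not say how operators and assessors are spread over clinics.

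This goes beyond selection bias, which concerns who enters each group. Clinic, operator and assessor effects would remain even if the two groups had identical patients. The primary comparison and every secondary and exploratory one are affected, and once data have been collected under this scheme no model can undo the aliasing.

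**Working it through.** **The plan's own figure.** Section 2.6.1 uses d = 0.56, α = 0.05 and 80% power; Section 2.6.2 makes all tests two-sided.
- Normal approximation: n = 2 × (1.960 + 0.842)² / 0.56² ≈ 50.1, so 51 per group.
- Exact two-sample t-test: 51.03, so 52 per group, 104 in all (power 80.7%). The stated 104 reproduces.
- Dropout: 104 / 0.9 = 115.6, so 116. The target of 120 is a rounding up.

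The calculation treats all patients as independent, with no clinic effect.

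**Can needle and clinic be separated?** A model with an intercept, needle and three clinic indicators has 5 columns. Because needle is the sum of the indicators of its two clinics, the rank is 4. The needle coefficient cannot be estimated beside fixed clinic effects. This needs no assumption.

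**How large could the effect be?** Inputs:
- SD of NRS change: the source trial in Section 2.6.1 gives 2.74 − 1.76 = 0.98, and 0.98 / 0.56 = 1.75. That trial was in chronic LBP at 3 weeks, so applying it to immediate change in acute LBP is an assumption.
- Patients per clinic: 30, assuming 60 per group split evenly. Only the 60 is stated.
- Clinic ICC: not given; 0.01, 0.05 and 0.10 are assumed.

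Formulas:
- Between-clinic SD: s = 1.75 × √ICC. The SD of a two-versus-two difference in clinic means is √(s²/2 + s²/2) = s.
- Design effect: DE = 1 + 29 × ICC. Effective n per group: 60 / DE.
- True type I error: 2 × [1 − Φ(1.96 / √DE)], checked by 20,000 simulated studies per setting.

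| Assumed ICC | SD of contrast due to clinics (NRS points) | DE | Effective n per group | Type I error, formula | Type I error, simulated |
|---|---|---|---|---|---|
| 0.01 | 0.18 | 1.29 | 46.5 | 8.4% | 8.4% |
| 0.05 | 0.39 | 2.45 | 24.5 | 21.0% | 20.8% |
| 0.10 | 0.55 | 3.90 | 15.4 | 32.1% | 33.2% |

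The simulation is slightly higher at ICC 0.10 because two clinics per group understate the clinic variance in the pooled SD. With 26 per clinic (the 52 per group of the calculation) the simulated errors are 8.0%, 19.2% and 30.6%. For scale, the t-test allows only for a sampling error of 1.75 × √(2/60) = 0.32 points, and the target difference is about 1 point.

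**Would a clinic-level analysis help?** Comparing four clinic means leaves 2 df. In SD units the standard error is √v with v = ICC + (1 − ICC)/30, and the noncentrality is 0.56 / √v. With unlimited patients per clinic, v tends to ICC.

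| Assumed ICC | Power, 30 per clinic | Power limit, unlimited patients |
|---|---|---|
| 0 | 40% | – |
| 0.01 | 33% | 79% |
| 0.02 | 29% | 56% |
| 0.05 | 21% | 30% |
| 0.10 | 16% | 18% |

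This analysis keeps the type I error near 5% when clinic effects are random, but it does not remove a systematic difference between the pairs of clinics. It is not planned.

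**The case against.** Four defences deserve a hearing.

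First, the study is exploratory, and Section 3 concedes selection bias and asks for randomised trials of needle length. A reader might infer that the protocol ignores the limits of its allocation; it does not. But nowhere does it say that clinic and needle effects are inseparable, and Sections 2.1 and 2.5.1 still attribute the difference to needle length.

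Second, the sites share operator training (Section 2.3.1), a defined goniometer method (2.5.2.1), a common assessment protocol with uniform assessor training (2.5.2.3), and the same device and solution (2.4). These may well make clinic effects small. That stands, and it is why the error rates are illustrative. It does not break the aliasing, and assessors remain unblinded.

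Third, a reader might infer that the study could never inform on needle length, even with unlimited patients. That goes too far. With two clinics per group a clinic-level analysis exists, and at an ICC of 0.01 its power limit is 79%. It is unplanned and weak at the planned size. Likewise, that each operator rates only one needle is an inference, since operator numbers and workplaces are not stated.

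Fourth, since all clinics use both needles, a reader might infer that comparing within clinic would cure the problem. It would not by itself. Needle choice follows the clinical situation, and the Introduction and Section 3 say that the shorter needle may not suffice where soft tissue is thick. Within a clinic the two needles may therefore go to different patients. The present scheme does not avoid this either, but any remedy has to address it.

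**Conclusion.** The concern holds. The aliasing of needle with clinic follows from Sections 2.1 and 2.3.2 without any assumption. The tests in Section 2.6.2 carry no clinic term, and its conditional adjustment for baseline variables cannot remove a clinic effect. The inflation of the nominal 5% error to about 8%, 21% or 32–33% rests on assumed ICCs of 0.01, 0.05 and 0.10 and on 30 patients per clinic. The conversion to NRS points (0.18 to 0.55) also rests on the SD of 1.75 borrowed from a chronic-LBP trial. If clinics do not differ at all, the planned test keeps its 5%, but these data could not show that the two pairs of clinics are alike apart from the needle. The defect touches the main comparison and cannot be repaired after data collection, so it should be settled before recruitment.

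**What to change.** Let every clinic contribute cases of both needle types. One way that keeps the extraction scheme is to swap each clinic's designated extraction needle once, at half of its recruitment, with two clinics starting on each type (about 15 cases per needle per clinic if there are 30 per clinic). This changes which cases are extracted, not how patients are treated. Rewrite the sixth inclusion criterion to match, and analyse within clinic with clinic as a fixed effect.

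Because needle choice depends on the clinical situation, also prespecify adjustment for baseline NRS and for collected variables likely to drive the choice (height and weight, or BMI). State that residual confounding by indication remains.

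Cost: no extra patients, and 3 df for clinic. An IRB amendment is needed, since Section 2.8.1 reports approval, and a registry amendment. A calendar-period effect is possible but is balanced by the two starting orders. Section 2.1 reports that nobody had been recruited when the manuscript was submitted; the current status should be checked.

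If the two/two split is kept, state in Sections 2.5.1 and 3 that needle and clinic effects cannot be separated, report the result as a comparison of clinic groups, and draw no conclusion on needle length. That costs only wording.
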